### **5.1.3 Pregnancy and Birth Control**

The potential risk to patients who conceive or are pregnant whilst taking study medication is not known, although reproductive toxicity has been reported in animals administered with either gefitinib or cediranib. Women of childbearing potential will be asked to take a pregnancy test by a healthcare professional at the screening assessment within 14 days of starting trial treatment.

Women of child bearing potential will be defined as all female trial participants who are not postmenopausal. Postmenopausal females are defined as:

- Natural menopausal with menses >2 years ago
- Radiation-induced oophorectomy with last menses > 2 years ago
- Chemotherapy-induced menopause with 2 years interval since last menses

- 
- Serum follicle stimulating hormone, luteinising hormone and plasma oestradiol levels in the postmenopausal range for the institution
  - Bilateral oophorectomy or hysterectomy

## Contraception

Female patients on the study must be post-menopausal, surgically sterile, sexually abstinent or use two reliable forms of contraception from starting cediranib and/or gefitinib and for 2 weeks after the last dose. Reliable methods of contraception should be used consistently and correctly, acceptable methods include barrier methods, implants, injectables, combined oral contraceptive methods, some IUDs, or partner had a vasectomy.

Male patients must use a barrier method of contraception from starting trial medications and for 2 weeks after the last dose.

In the event of a pregnancy occurring on the trial, please report immediately to the UCL CTC (see [section 10.6](#) Pregnancy reporting).

## 5.2 Pre-randomisation evaluation

Patients must give written informed consent before any trial specific screening investigations may be carried out. The following assessments or procedures are required to evaluate the suitability of patients prior to entry:

- Confirmation (histological/cytological) that patient has glioblastoma (WHO grade IV)
- Within 7 days prior to randomisation:
  - Brain Tumour assessment: MRI scan of the tumour region, where the tumour is the largest. –See [section 7.7](#) (Imaging) for the list of required scans.
  - Demographic details including date of birth, sex, and race
  - Relevant medical and surgical history, including previous hypertension, ongoing medication and documentation of baseline symptoms
  - Physical examination: height and weight, vital signs (including pulse, lying and 5 min standing blood pressure, respiratory rate and temperature)
  - ECOG performance status
  - Karnofsky performance status

- Mini-mental status exam
- Neurological examination
- Full blood count (FBC)
- Serum biochemistry: sodium, potassium, urea, creatinine, phosphate, total protein, albumin, globulin, adjusted calcium, total bilirubin, alkaline phosphatase, AST and/or ALT, LDH and gamma-GT.
- Clotting function tests (PT/APTT)
- Thyroid function tests
- Urinalysis: dip-stick test for protein. If a patient has two consecutive urine protein measurements of greater than one plus (+) taken no less than 1 week apart then measure urine protein:creatinine ratio or collect a 24-hour urine for total protein. A urine protein/creatinine ratio of 0.15 (urine protein and urine creatinine expressed in mg/dl) approximates a 24-hour urine protein of 150mg/24 hours or 0.15 g/24 hours, which is the upper limit of normal.
- Pregnancy test (if applicable – i.e females of child bearing potential (see [section 5.1.3](#)))
- ECG with estimation of QTc interval (see Appendix 7)

### **5.3 Screening Log**

A screening log should be maintained by the site and kept in the Investigator Site File. This should record each patient screened for the trial and whether or not they were randomised to the trial. If they were not randomised the reasons should be given. The log should be sent to UCL CTC when requested with patient identifiers removed prior to sending.

---

## 6.0 Randomisation procedures

### 6.1 Randomisation

Patient randomisation will be performed centrally at the UCL CTC, after the relevant site has faxed the fully completed randomisation form to UCL CTC and it has been checked by a trained UCL CTC staff member to confirm eligibility and informed consent. Randomisation must be performed prior to commencement of any trial treatment. Patient randomisation will be performed using an interactive web-based recognition system (Cenduit IWRS), with a link to an Access randomisation programme. Randomisation will be undertaken using minimisation, and stratified by age (<65 or ≥65yrs) and resection for the recurrent disease (previous resection / no previous resection), Karnofsky performance status (>80 / ≤80). Within each stratum patients will be randomised in a 1:1 ratio to the treatment arms.

Sites should ensure that the following have been completed before randomising:

- Patient consent form must be signed
- Pre-randomisation evaluations should be carried out at sites as detailed in [Section 5.3](#) (following consent if not done routinely)
- The randomisation form must be fully completed prior to faxing the UCL CTC
- Screening MRI scan must have been completed (a copy should be sent to UCL CTC following randomisation, see [Section 7.7](#))

On receipt of completed randomisation form at UCL CTC:

- If the patient is confirmed as eligible, a patient trial number will be assigned at UCL CTC
- The UCL CTC will then randomise the patient on the Cenduit interactive web-based response system (IWRS). The IWRS will send an e-mail to site staff and pharmacy, notifying them of medication codes which correspond to stock sufficient to cover the patient's first 6 weeks of treatment i.e. 6 weeks of daily cediranib plus daily gefitinib/placebo. Site staff will be responsible for using IWRS for drug resupply visits (for more information, refer to the IWRS user manual).
- A unique patient trial number will be assigned. The UCL CTC will fax a confirmation form to the site's lead research contact and also the lead pharmacist, confirming both the patient's inclusion in the trial and their trial number. The site should then enter the patient's trial number in the randomisation CRF and arrange for the MRI scan to be sent to the UCL CTC.

- The original randomisation form should be posted to UCL CTC and a copy kept at site.
- Case report forms will be sent by UCL CTC to the main contact at site.

|                                        |                                              |
|----------------------------------------|----------------------------------------------|
| Randomisation telephone number: | [name]                          |
| Randomisation fax number:       | [name]                          |
| Office hours:                   | 09:00 to 17:00 Monday to Friday
(UK Time) |

Once a patient has been randomised onto the trial they must be provided with the following:

- A copy of their signed consent form(s) and patient information sheet
- A patient contact card. Site on-call contact details for out-of-hours medical care must be added to this card and patients informed to carry this with them at all times while on the trial

The baseline assessment should be carried out on the day that study treatment begins, which must be within 2 weeks of the screening assessment. If screening laboratory and ECG tests were carried out more than 7 days prior to baseline these should be repeated at baseline. The baseline MRI should be within 7 days before randomisation. Baseline assessments should be carried out as per [Section 8.1](#) and [Section 5.2](#).

## Interactive Web-based Recognition System (IWRS)

The IWRS will be used for randomised allocation, trial medication assignment, initial drug supply and resupply, discontinuation from study treatment, emergency code breaks (i.e. unblinding) and trial drug shipment confirmation. The IWRS technology will be managed and maintained by Cenduit, in collaboration with Fisher Clinical Services. The system is accessible via the internet 24 hours a day, 7 days a week. The IWRS user manual will be provided to all sites, and contains full details regarding the operation and use of the system.

## 6.2 Trial drug supply

### 6.2.1 Initial trial drug supply

An initial supply of cediranib, gefitinib and placebo will be shipped to each site by Fisher upon site activation by the UCL CTC, via the Cenduit/Fisher IWRS. This initial supply is prompted by the UCL

CTC using the IWRS to confirm each site activation. Please see the Pharmacy Site File, IWRS User Guide, and Pharmacy Manual for further details.

### 6.2.2 Resupply of cediranib & gefitinib/placebo

Resupply of cediranib and gefitinib/placebo will be managed automatically by IWRS, which will count down as patients are allocated trial stock. A resupply shipment will be triggered once a site's stock becomes sufficiently low. However, site pharmacies will be able to manually request additional stock via the IWRS. For exceptional circumstances (e.g. a site intending to randomise several patients on one day), **sites will need to provide the UCL CTC with a week's notice where possible**, so that IWRS is able to ensure that sufficient stock is provided to meet the site's dispensing requirements.

## 7.0 Trial Treatment

### 7.1 Treatment summary

For the purpose of this protocol, the active IMPs are cediranib and gefitinib, with gefitinib-matched placebo.

Enrolled subjects will be randomised to receive **either** cediranib 30mg od orally and gefitinib 500mg od orally **or** cediranib 30mg od plus placebo. Each cycle of treatment lasts 6 weeks.

Treatment will continue until confirmation of progression as defined in 2.6.1.1, patient decision or the development of unacceptable toxicity (if there is radiological progression only treatment can continue if the investigator has the opinion that the patient is receiving benefit. It is not compulsory to stop trial treatment at any indication of radiological progression, even at confirmed radiological progression on multiple scans if it is felt that the patient is receiving benefit. Investigators should be wary of pseudoprogression on MRI scans.).

If none of the above are thought to have occurred on the last day of the treatment cycle, the patient will start the next cycle of treatment the following day. Treatment pauses of up to 14 days are permitted (21 days are permitted in consultation with the CI) but should be recorded on the next CRF. Treatment delays of longer than 14 days (or 21 days in consultation with the CI) will result in patient withdrawal from the study.

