A maximum of a 14-day (21-day in consultation with the CI) delay in dosing for cediranib is permitted. If a longer interruption is required due to unresolved toxicity, cediranib should be discontinued. In addition, there are certain circumstances in which study medication should be permanently discontinued (see [section 13.1](#)).

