## 7.4.2 Management of toxicity attributable to gefitinib

Dose interruptions should be used as the first approach to managing toxicity and dose reduction may be considered.

The events for which de-escalation of the gefitinib dose is recommended include:

- CTCAE grade 3 or higher toxicities of duration >3 days that are considered to be related to study treatment that are not responding to maximal supportive care within 48 hours, at the discretion of the investigator.

With the EXCEPTION of

- Rash ([section 7.4.2.1](#))
- Interstitial lung disease ([section 7.4.2.2](#))
- Diarrhoea ([section 7.4.3](#))

the following management plan should be followed for management of toxicity attributable to gefitinib:

Dose interruptions should be used as the first approach to managing toxicity. For CTC Grade 3 or more, dosing with gefitinib should be interrupted. Gefitinib dosing may be withheld for up to 14 days (or 21 days in consultation with the CI) for management of toxicity. If a longer interruption is required due to unresolved toxicity, gefitinib should be discontinued.

- If the symptoms promptly resolve to grade 1 or below with supportive care, consideration should be given to continuing the same dose of gefitinib along with appropriate continuing supportive care
- If the symptoms of the toxicity are considered related to gefitinib and do not resolve to grade 1 or below with maximum supportive care and following a dose interruption of up to 14 days (or 21 days in consultation with the CI), the next dose level of gefitinib below that being dosed should be instituted
- If the symptoms do not resolve and it is considered medically appropriate, investigators may choose to permanently discontinue gefitinib

For patients who have multiple low-grade adverse events short dose interruptions (ie, 2- 5 days) of the gefitinib tablets may help. Treatment can be restarted on resolution at the same dose

One dose reduction for the gefitinib treatment will be permitted during the study. No re-escalation of dose is permitted.

A maximum of a 14-day (21-day in consultation with the CI) delay in dosing for gefitinib is permitted. If a longer interruption is required due to unresolved toxicity, gefitinib should be discontinued. In addition, there are certain circumstances in which study medication should be permanently discontinued (see [section 13.1](#)).

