### k) Assessment dates during trial treatment

The cycle start assessment should be carried out on the day the patient begins the next cycle of study treatment. **Clinic assessments and MRI assessments will occur at the specified time points irrespective of trial treatment holidays.** E.g a 6 week cycle may only contain 3 or 4 weeks of trial treatment if a patient has had a trial treatment holiday during that cycle. If either treatment is delayed for more than 14 days due to toxicity (or 21 days if the CI has permitted a 21 day treatment holiday), the patient should cease taking the medication and continue with the cycles of the other study treatment. If both the study treatments are delayed for more than 14 days due to toxicity (or 21 days if the CI has permitted a 21 day treatment holiday), the discontinuation assessment should be performed and the patient withdrawn from the trial.

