## 13.0 Withdrawal of patients

In consenting to the trial, patients are consenting to trial treatment, assessments, follow-up and data collection.

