### 13.1.2 Procedures for discontinuation from treatment

Patients who discontinue the trial treatment should always be asked about the reason(s) for their discontinuation and the presence of any adverse events. If possible, they should be seen and assessed by an investigator(s). The patient should return investigational products.

If all study treatment is stopped during the study, the Principal Investigator/Sub investigator will perform the best possible observation(s), test(s) and evaluation(s) as well as give appropriate treatment and all possible measures for the safety of the patient. In addition, they will record on the Case Report Form (CRF) the date of withdrawal, the reasons, and treatment at the time of withdrawal.

If only one study treatment is stopped during the study, the patient will continue with the trial assessments as before. Reasons for stopping the first drug must be recorded on the CRF. The discontinuation assessment is only to be carried out upon discontinuation of both trial drugs.

At withdrawal, all on-going SAEs must be followed until resolution, unless in the Investigator's opinion, the condition is unlikely to resolve due the patient's underlying disease.

All new AEs occurring for up to 30 days after the last dose of any study medication must be recorded in the CRF. Ongoing AEs thought to be caused by trial treatment will be followed up until resolution or death. All SAEs occurring up to 30 days after the last dose of any study medication must be followed until resolution.

Patients who are not receiving treatment, but are being followed up for tumour assessments should also be followed up for procedure related SAEs, these should be reported on an SAE report form (see [section 10.2.2](#) SAEs). AE collection beyond the 30 days post treatment is not required for patients who have progressed and are being followed up for survival only.

For patients who are withdrawn from study treatment for reasons other than disease progression every effort will be made to continue with collecting the trial MRI scans every 6 weeks. Follow up clinic assessments should be carried out every 6 weeks as detailed in [section 8](#).

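### Section 7.1 ends study participation after any long treatment delay, while other sections stop only the delayed drug; its wording, like that of 8.2 k, also leaves PFS follow-up open to misreading

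*Protocol*

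**What the plan says.** Section 7.1 permits treatment pauses of up to 14 days, or 21 days in consultation with the Chief Investigator, and then says: "Treatment delays of longer than 14 days (or 21 days in consultation with the CI) will result in patient withdrawal from the study". It does not say whether one drug or both must be delayed, or whether the delay must be due to toxicity.

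Section 8.2 k separates two cases, both for toxicity. If either drug is delayed beyond the limit, "the patient should cease taking the medication and continue with the cycles of the other study treatment". If both are, "the discontinuation assessment should be performed and the patient withdrawn from the trial".

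The toxicity sections follow the single-drug logic. Section 7.4.1: "If a longer interruption is required due to unresolved toxicity, cediranib should be discontinued". Section 7.4.2: "If a longer interruption is required due to unresolved toxicity, gefitinib should be discontinued". Section 13.1.2 adds: "If only one study treatment is stopped during the study, the patient will continue with the trial assessments as before".

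Section 13.1, which concerns withdrawal from trial treatment, gives a toxicity-related IMP delay beyond the same limits as a possible reason for withdrawing a patient from all trial treatment.

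On follow-up, section 13.0 opens by saying that in joining the trial "patients are consenting to trial treatment, assessments, follow-up and data collection". For patients who stop treatment for reasons other than progression, 8.2 h requires 6-weekly follow-up to progression or death. Sections 8.2 f and 13.1.2 both say that "every effort will be made to continue with collecting the trial MRI scans every 6 weeks".

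**The concern.** Two problems sit in one sentence of 7.1.

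The first is a conflict over treatment. Suppose a patient has one drug held for longer than the limit while the other is tolerated. Under 7.1 the patient leaves the study. Under 8.2 k the patient continues on the other drug. Under 13.1 the same event may justify stopping everything. Sites would then treat the same event differently, and in a trial of this size such differences affect exposure and the reading of tolerability.

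The second is wording that touches the primary endpoint. PFS is analysed in all randomised patients (16.2), and those without an event are censored at last contact (16.3). If a site takes withdrawal from the study or trial to mean that scans and visits stop, the patient is censored at a toxicity-driven moment. Gefitinib has toxicity of its own and shares diarrhoea with cediranib (2.3.2, 7.4.3), so such delays may be more frequent on the combination. Censoring could then be informative and unequal between arms.

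**Working it through.** **1. The delay rules side by side**

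| Section | Delay covered | Consequence |
|---|---|---|
| 7.1 | Treatment delay, drug and cause not specified | Withdrawal from the study |
| 8.2 k, first case | Either drug, toxicity | That drug stops, the other continues |
| 8.2 k, second case | Both drugs, toxicity | Discontinuation assessment, then withdrawal from the trial |
| 7.4.1 | Cediranib, toxicity | Cediranib stops |
| 7.4.2 | Gefitinib, toxicity | Gefitinib stops |
| 13.1 | An IMP, toxicity of grade 3 or above | Possible reason to withdraw from all trial treatment |
| 13.1.2 | One drug stopped | Trial assessments as before |

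For a long delay of one drug, 7.1 cannot be applied together with 8.2 k, 7.4.1, 7.4.2 and 13.1.2. For both drugs, 7.1 and 8.2 k agree on the outcome but share the loose term. For delays not due to toxicity, only 7.1 speaks.

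**2. What withdrawal from the study or trial means**

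- Section 13.1 places the long toxicity delay under withdrawal from trial treatment.
- Section 14.1 uses withdrawal from the trial, for a treatment holiday that is extended, to fix the date on which treatment finished.
- Section 13.2 makes the end of data collection a separate step that needs an explicit statement by the patient.
- Sections 8.2 f, 8.2 h and 13.1.2 continue MRI and 6-weekly follow-up after a stop for reasons other than progression.

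Taken together, these mean that treatment ends and follow-up goes on. Neither 7.1 nor 8.2 k says so where the instruction is given, and section 13 has no category called withdrawal from the study.

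**3. Size, as sensitivity only**

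Inputs from 16.1: medians of 4 and 6 months, so HR = 4/6; one-sided type I error 10%; power about 80%; 110 events.

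Reproducing the plan by Schoenfeld's formula:

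events = 4 × (z₀.₉₀ + z₀.₈₀)² / (ln HR)² = 4 × (1.2816 + 0.8416)² / 0.4055² = 109.7, rounded up to 110. This matches the plan.

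Power = Φ(½√events × |ln HR| − z₀.₉₀). With 110 events: Φ(5.244 × 0.4055 − 1.2816) = Φ(0.845) = 80.1%.

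The documents give no rate of long delays or of follow-up lost because of them. The fractions below are therefore assumptions.

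| Assumed share of events unobserved | Events | Power |
|---|---|---|
| 0% | 110 | 80.1% |
| 5% | 104.5 | 78.5% |
| 10% | 99 | 76.9% |
| 20% | 88 | 73.2% |
| 30% | 77 | 69.1% |

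The table shows loss of information only. It does not measure bias from informative censoring.

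**The case against.** The best defence on treatment is that 7.1 is a summary and its sentence follows text on starting the next cycle. Read as a delay of trial treatment as a whole, it agrees with the both-drugs case in 8.2 k. That reading is reasonable, but 7.1 does not state it, and 13.1 refers to an IMP delay in a list of reasons for stopping all treatment. The conflict stands.

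The defence on follow-up is stronger. A reader might infer that the protocol orders PFS follow-up to end after a long delay. The documents do not support that. Sections 13.1 and 14.1 use the language of withdrawal for the end of treatment, 13.2 reserves the end of data collection for the patient's own decision, and 8.2 f, 8.2 h and 13.1.2 schedule the follow-up. Section 13.0 says what patients consent to; it does not define study withdrawal. The discontinuation assessment required by 8.2 k leads in the schedule to long-term follow-up, which includes MRI. What remains is a risk of misreading.

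Three further inferences also go too far.

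- *The ITT analysis is broken.* Censored patients remain in the ITT population; the possible problem is informative censoring.
- *The hazard ratio would be biased by a stated amount.* In simulation with assumed withdrawal of 5% on control and 15% on the combination, the HR moves from about 0.69 to 0.66–0.67 only if the hazard is assumed to double after withdrawal. Without that assumption it is 0.66 either way. The documents supply neither the rates nor the doubling.
- *Only two events can be lost, since 110 are needed from 112 patients.* That thin margin is a separate feature of the sample size.

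**Conclusion.** The contradiction over single-drug delays is established by the text: 7.1 conflicts with 8.2 k, 7.4.1, 7.4.2 and 13.1.2, and 13.1 adds a third version. No view is taken here on which rule is right.

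The follow-up point holds as a wording risk. The wider protocol indicates that MRI and follow-up continue, but 7.1 and 8.2 k use terms that a site could take as ending them. If that happened, events would be lost and censoring could depend on toxicity and differ by arm. Its size cannot be computed from the documents. The fall in power from 80.1% to 76.9% rests on an assumed 10% loss of events, HR 4/6 and one-sided 10% error. The planned 110 events and 112 patients do not change.

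**What to change.** Reconcile 7.1 with 8.2 k, 7.4.1, 7.4.2, 13.1 and 13.1.2, so that each gives the same consequence when one drug is delayed beyond the limit and the same consequence when both are. State also whether delays not due to toxicity are covered. The choice of rule belongs to the sponsor and the Chief Investigator.

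In 7.1 and 8.2 k, add that whatever treatment decision applies, MRI and follow-up continue as set out in 8.2 f, 8.2 h and 13.1.2, unless the patient withdraws consent to data collection under 13.2. It is not enough to replace withdrawal from the study in 7.1 with discontinuation of trial treatment, because that would still contradict 8.2 k for a single drug.

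The cost is a protocol amendment to wording and a note to sites. No visits, scans or patients are added, because the follow-up is already scheduled.
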